#### Data storage and security

We will save two types of data separately. First, we will save metadata in a PostgreSQL database stored on the same encrypted server as the state machine. This will include all data generated by the software that runs the state machine (e.g., timestamps and completion logs). The metadata will also contain participants’ email address, participant IDs, group assignment information (i.e., BA or CR, and training or test), task and questionnaire batch access links, e-couch tokens, identity check assignments and reasons, withdrawal or exclusion reasons, consent information, and documentation of completion of task and questionnaire batches (including individual tasks), each with an associated timestamp. A subset of the metadata information is also saved in participants’ individual metadata files.

Second, we will save data from self-report questionnaires and behavioral tasks in time-stamped files after completion (or early termination) of each task or questionnaire batch. Each file will include the participant’s participant ID and the name of the relevant task or questionnaire batch. Data from training and test groups will be stored in two separate locations throughout the study.

Task and questionnaire data will be stored on both the primary encrypted server and on a second, separate Princeton server that is not accessible via the Internet. We will routinely verify that all task and questionnaire data have been successfully saved to the second server; once verified, we will delete the corresponding task and questionnaire data files from the primary server that is connected to the internet, as a precautionary data-security measure in case the primary server were compromised. We will additionally use command line tools to back up task and questionnaire data to another separate location on the second server.

Data collected while participants engage with the e-couch program will be stored on e-couch’s secure servers in accordance with their privacy policy https://ecouch.com.au/info/privacy. We will download pseudonymized usage data (that is, identified only by participants’ e-couch tokens) from the e-couch administration interface weekly. These data will then be transferred to Princeton University’s secure servers.

We will advertise and recruit participants via ResearchMatch (see section 20, *Recruitment*). Email addresses of participants who express interest in our study on ResearchMatch can only be exported jointly with other information they provided to ResearchMatch, such as name, address, demographics, veteran status. ResearchMatch requires that these data are only saved on encrypted devices. Accordingly, we will download and save these data directly to an encrypted device. We will then delete all information except the email addresses, which are needed to send participants the study information and a link to the screener.

### Statistical methods (27)

The goals of our study are multifaceted. First, we aim to build algorithms that predict who would benefit from CBT-based interventions for depression, and specifically whether behavioral or cognitive interventions would be more beneficial for a given individual. Second, we are interested in testing whether learning and decision-making capacities assessed through our behavioral tasks improve the predictive accuracy of these algorithms – if so, this would suggest that the cognitive mechanisms assessed through the tasks may be related to the processes involved in CBT. Finally, we seek to uncover how these learning and decision-making capacities influence (i.e., moderate) participants’ responses to the interventions and whether changes in some capacities mediate the responses. In developing these algorithms, we aim to ensure that their application is feasible in a real-world clinical setting, requiring minimal additional time or resources. We also seek to ensure that our results are as reliable and robust as possible.

One challenge we face with these goals is that no prior evidence exists regarding our task-derived measures, their predictive power for differential outcomes of BA and CR, and their variation in interactions with clinical and sociodemographic variables. Without such prior data, it is difficult to anticipate the precise nature of these interactions or to identify the most adequate and least biased analytical approach.

A further challenge arises due to different adherence levels across participants which dilute moderation effects and weaken differential prediction effects in intention-to-treat (ITT) analyses. To address this, we plan to incorporate adherence levels into our models and adjust for potential biases that may arise (see Section 27d, *Methods for any additional analyses*). We are not aware of any study in the mental health literature that has included predicted adherence scores in individual-level differential prediction models, but will expand on relevant prior work suggestions in the literature (82).

To address these challenges while ensuring that our final results are not influenced by different types of data leakages, we will randomize participants into training and test datasets (2:1 ratio) at the time of consent to the main study. This will allow us to conduct a series of exploratory analyses on the training dataset and finalize our precise analytic approach using power and sensitivity analyses.

We will then preregister all hypotheses, algorithms and a code pipeline before accessing and applying them to the test dataset.

While our test dataset does not constitute a fully external dataset, as highlighted in guidance on prediction model evaluation and generalizability (83, 84), this approach has the following advantages given our dataset size:

Preventing data leakage, which often occurs with improper cross-validation on a single dataset (85).Allowing for tuning of hyperparameters such as decision thresholds.Allowing to explore more advanced statistical methods that can then be validated.Safeguarding against false positive results.Ensuring that researchers’ decisions based on observing the training data do not result in bias or overfitting of the test data.Replication of results.

Our preregistration will include all required details including, among others, the statistical approach, effect size, significance levels and adjustments, as well as code implementing these.

We acknowledge that our two-step approach with a detailed pre-registration of the analysis plan for the held-out test dataset done after data collection (but prior to observing these data) is non-traditional in the context of clinical trials. However, given the complexity of the statistical approach we are taking, the size and thus power of our dataset, the timeline we have to collect the data, and a setup where we can ensure that the held-out test data are not observed by a human during the study, we believe that this is the most useful methodological approach we can employ to achieve robust results and inform subsequent research.

We outline below the most appropriate approaches we have so far identified for our exploratory analyses for our main research questions. Because of the rapid evolution of the literature and recommendation on analysis methods we plan to conduct, we may use a different approach if it is clear that a more suitable and less biased approach is available at the time of analysis of the training data.

### Statistical methods for primary outcomes (27a)

#### Preprocessing of data

We will compute summary scores for all questionnaires in accordance with scoring procedures outlined in the original validation papers (see Section 25, *Data collection method* for the list of questionnaires and references). For behavioral task data, computational models will be applied where appropriate to infer underlying cognitive mechanisms and enhance measurement reliability (see Section 25, *Data collection method* for task descriptions and citations of papers describing the computational models corresponding to each task). Our computational modeling approach for task data includes model comparison, parameter estimation, model recovery, parameter recovery and posterior predictive checks of the winning model.

All data preprocessing steps will be treated as components of the modeling pipeline and performed within each training fold only, to prevent information leakage. Continuous predictors will be centered and scaled using parameters estimated from the training fold and then applied to the corresponding validation fold. Missing predictor data will be handled via multivariate imputation by chained equations (MICE), with imputation models fit within training folds only, as described in section 27c, *How missing data will be handled*. Because the study is not multi-site, no harmonization across sites is required.

We will preregister the code for all preprocessing steps before applying them to the test dataset.

#### Primary analyses: predicting response to CBT-based interventions

Our primary analytic goal is to predict who will benefit from CBT-based interventions and who might benefit more from BA versus CR. In line with recommendations by (84), predictors will be exclusively based on variables collected during the baseline assessment and their definition or computation will not be dependent in any way on outcome variables. Similarly, outcomes will be defined independent of any predictor variables (e.g., we will not use change scores as outcomes).

Model development will be conducted exclusively within the training data using an internal validation framework. Specifically, we will use nested, repeated 10-fold cross-validation, with the full procedure repeated 100 times to improve the stability of performance estimates. Identical cross-validation splits will be used across all candidate models to enable fair model comparisons.

To develop our models, we will first perform systematic variable selection and exploratory modeling on the training dataset using cross-validation to assess consistency and prevent overfitting. We will add to the models groups of related predictors (such as demographic variables, clinical variables, task-derived variables) that would be presumably assessed jointly in a clinical setting and subsequently use automated feature selection and regularization to determine which predictors to include in the final model. Predictor selection will be treated as part of the model development process and conducted exclusively in the training data. The finalized predictor set for each model and time point will be fixed and preregistered prior to confirmatory evaluation on the held-out test data.

We will evaluate multiple model classes, including penalized regression approaches (e.g., lasso and elastic net) and random forest models. Hyperparameter tuning will be performed exclusively within the training data using a nested cross-validation framework, with all tuning restricted to inner folds. Performance metrics will include balanced accuracy for classification models and mean squared error and *R*^2^ for regression-based models. Model performance will be summarized using pooled out-of-sample predictions across all cross-validation folds and repetitions. For classification models where AUROC will be used as the primary discrimination metric, DeLong’s method (86) will be used to obtain confidence intervals and to test differences in AUROC between models. Calibration will be performed within the nested cross-validation framework using out-of-fold predictions from the inner loop – that is, using predictions that are generated for participants in the outer-training fold by a model that did not include those participants during fitting, ensuring no information leakage. A calibration model (e.g., Platt scaling for classifiers) will then be fitted to these predictions, where appropriate. We will report mean absolute prediction error and quantify uncertainty around individual predictions. The methods to generate prediction uncertainty will be determined and set during model development and applied without modification to predictions from the held-out test dataset. The finalized modeling pipeline, including the internal validation strategy, preprocessing steps, target optimization metric, and any hyperparameter tuning procedures, will be fixed and preregistered prior to confirmatory evaluation on the held-out test dataset.

Following confirmatory evaluation of the preregistered models, we will conduct *post-hoc* interpretability analyses using SHAP values to aid in understanding the contribution of individual predictors to model predictions (87).

More specifically, we will first create predictive models using only clinical and demographic variables, which will constitute our baseline models. For the preregistration, we will choose one baseline model considering predictive power, stability, clinical feasibility and interpretability. Preregistered analyses of the test data will assess the extent to which this model improves predictive power as compared to chance.

Second, we will add task-derived variables from each task separately to the baseline model to test whether these variables improve the predictive accuracy. For each set of task variables that we find to improve predictive accuracy, we will preregister the corresponding analyses for confirmation in the test dataset. We take this single-task approach as we consider each task as a separate instrument to be tested for efficacy independently, and to improve clinical feasibility (as one 15-minute task is clinically more feasible than a two-hour task battery) and interpretability (as some tasks assess correlated features, so combining them could obscure which variables drive the effects).

We will take this two-step approach both when examining how well we can predict whether an individual will respond to CBT-based interventions, and whether we can differentially predict whether they will benefit more from BA vs CR. For algorithms aiming to predict depression scores at week six after engaging with any CBT-based interventions, the final outcome will be out-of-sample predictive accuracy above chance (for the baseline model) or above the baseline model (for models including task data). For algorithms predicting differential outcome for behavioral vs. cognitive interventions, we will train algorithms for each arm separately. Following the approach of the personalized advantage index (PAI; 88, 89), we will use the model to predict for each participant the outcome for the intervention they received (using models trained on data not including this participant) and for the one they did not receive (counterfactual outcome). The final outcome will constitute whether individuals who were predicted to have received their more beneficial outcome have lower depression scores at the 6-week mark than those who the algorithm predicts would have fared better from the other intervention (and how much that difference improves by adding in task parameters).

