#### Matrix reasoning task

The matrix reasoning task (79–81) will be included as a measure of general cognitive ability and to index attentional engagement across tasks. In this task, participants must solve a series of puzzles. On each trial, participants view a 3x3 matrix of abstract shapes, with one cell (the bottom-right) remaining empty. Participants are instructed to complete the matrix by identifying the missing element from four possible alternatives. To do so, participants must infer the underlying logical pattern, such as changes along the vertical, horizontal, or sequential dimensions, based on the arrangement of the other shapes. No feedback regarding correctness is given. The task has 12 trials and takes approximately 3 minutes to complete. Zorowitz et al. (81) reported good reliability and convergent validity of an open-access item bank of matrix reasoning tasks in large online samples, which is the version we will use in this study. We use different sets of stimuli when we repeat the task at different time points in the study (note: version 1.0 of this protocol used the same set of stimuli multiple times).

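### A learning task is credited with a mechanism if it beats a clinical/demographic model, although the general cognitive ability measured at baseline is left out of that comparison

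*Protocol article*

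**What the plan says.** Section 27a (Primary analyses) sets up two steps. In the first, "we will first create predictive models using only clinical and demographic variables, which will constitute our baseline models". In the second, "we will add task-derived variables from each task separately to the baseline model to test whether these variables improve the predictive accuracy". Success for a task model is out-of-sample accuracy above that baseline. The reasons given for testing tasks one at a time are clinical feasibility and interpretability, the latter "as some tasks assess correlated features, so combining them could obscure which variables drive the effects".

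Section 27 states what a gain would mean: "this would suggest that the cognitive mechanisms assessed through the tasks may be related to the processes involved in CBT". Hypothesis 1 in section 10 is that flexible, intact learning goes with better response to CBT.

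Section 25 describes the matrix reasoning task as "included as a measure of general cognitive ability and to index attentional engagement across tasks". Section 18 places it in the first baseline questionnaire batch, so it is available as a predictor. Symmetry span is collected as a measure of working memory. Both are listed among the behavioral tasks, and neither is placed in the reference model. The section on mechanisms of change (moderation and mediation) names no ability covariate.

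**The concern.** The planned comparison tests whether a task carries information beyond clinical and demographic variables. The mechanistic reading needs more: that the task carries information beyond what a generally able participant would show on almost any task. If more able people respond better to a self-guided program, and also score better on a learning task, that task will improve on the baseline even when the learning parameter plays no role of its own.

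The protocol measures this rival explanation at baseline but does not use it in the comparison. Because each task is added alone, matrix reasoning cannot stand beside a learning task in any of the stated models. At stake is whether support for Hypothesis 1 could be told apart from an effect of general ability.

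**Working it through.** **Plan's own figure.** The required development sample of 875 (section 19) follows from the shrinkage criterion n = p / [(S − 1) · ln(1 − R²/S)] with S = 0.9 and R² = 0.05. With p = 5, n = 5 / [(−0.1) · ln(1 − 0.0556)] = 875, an exact match. With p = 4 it is 700 and with p = 6 it is 1,050. The concern does not rest on this figure, but the figure is needed to cost the fix.

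**What the existing safeguards cover.**

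- *Early screen (section 25):* matrix reasoning fails only with fewer than three of 12 items correct or with very fast responding, and exclusion needs more than one failure among four checks. Differences in ability above that floor remain.
- *Task-specific flags (section 25) and sensitivity analyses (section 27d):* models with and without flagged participants, or a failed-check variable interacting with the task variables. These address attention, not ability.
- *Demographics:* education, income and occupation could enter the baseline model, as rough stand-ins for ability.

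Attention is therefore partly handled. General ability is not.

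**Size of a proxy gain.** Let r be the correlation of task and ability, β the standardised effect of ability on outcome, and let the task have no effect of its own. The population gain in R² over a baseline without ability is r²β².

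- r = 0.2, β = 0.1: 0.04 × 0.01 = 0.0004
- r = 0.3, β = 0.2: 0.09 × 0.04 = 0.0036
- r = 0.4, β = 0.2: 0.16 × 0.04 = 0.0064

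Suppose a matrix score correlating λ = 0.85 with ability is in both models. The gain becomes [βr(1 − λ²)]² / (1 − r²λ²). At r = 0.4 and β = 0.2 the numerator is (0.2 × 0.4 × 0.2775)² = 0.0222² and the denominator is 1 − 0.16 × 0.7225 = 0.8844. The gain is about 0.0006, so most of it goes but not all.

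**How often such a task would pass.** The simulation follows the planned type of evaluation: fit in training data, then test the gain in squared error on held-out data. Sample sizes are 1,500 × 0.8 = 1,200, split 2:1 into 800 and 400. Assumptions: linear models, a continuous outcome, a baseline severity effect of 0.4 SD, λ = 0.85, 2,000 runs, and a one-sided 5% test. With a clinical baseline only:

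| r | β | pure-proxy task passes |
|---|---|---|
| 0.2 | 0.1 | 5% |
| 0.3 | 0.1 | 7% |
| 0.2 | 0.2 | 10% |
| 0.3 | 0.2 | 16% |
| 0.4 | 0.2 | 23% |

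With the matrix score in the reference model and the task model, the rate is about 3% to 6% over the same range.

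A second simulation used the article's planning figures (1,000 training, 300 test), with ability explaining 2% to 5% of outcome variance and r of 0.3 to 0.5. It gave 10% to 29% without ability in the baseline, about 3% with an error-free ability score in it, and 4% to 9% with a score of reliability 0.7. With r = 0 the pass rate was also about 3%, so this held-out test runs slightly below its nominal level, and the excess comes from the shared ability.

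**The case against.** The strongest reply is that the plan's primary outcome is predictive accuracy. Each task is treated as a separate instrument, and for that purpose a gain that comes through ability is a real gain. This stands: a reader might infer that the primary prediction result is invalid, and the documents do not support that. The mechanistic sentence in section 27 is also hedged, and mechanisms have their own moderation and mediation analyses. That limits the weight of the point but does not remove it, because the section still links the gain to the task's mechanisms and those further analyses name no ability covariate.

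A reader might also infer far larger error rates. Testing the task's regression coefficient at n = 800 would give 48% (r = 0.3, β = 0.2) or 70% (r = 0.4, β = 0.2). That is not the planned evaluation, which judges preregistered models on held-out gain, so those rates do not describe this trial.

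Nor does it follow that one shared factor would credit every task and every hypothesis. Hypothesis 2 predicts better BA response from reduced anticipation with intact experience, a pattern that general ability does not obviously produce. An ability effect that is equal in both arms largely cancels in the BA-versus-CR difference.

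Matrix reasoning could itself be one of the tasks added separately. That would show whether ability alone predicts outcome, but it would not put ability beside a learning task.

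Finally, the introduction describes CR as relying on deliberative, cognitive learning, of which working memory may be a part. Requiring a gain beyond symmetry span could therefore over-adjust. This objection stands and shapes the fix.

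**Conclusion.** The point holds in a limited form. As stated, the comparison cannot separate a learning mechanism from general cognitive ability, although a baseline measure of ability is collected. The mechanistic reading of a gain in predicting overall response (Hypothesis 1) is therefore weaker than section 27 suggests. The prediction claim stands, and the BA-versus-CR contrast is less exposed.

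Over the assumed range, a pure-proxy task would pass a held-out test in about 5% to 23% of runs, against about 3% to 6% with the matrix score included. At the weakest inputs the excess is negligible. The article states neither the task-ability correlation nor the ability-outcome effect, so these are illustrations under assumptions and not estimates for this trial. The test-set analysis is still to be preregistered, so the remedy can be adopted without disturbing anything already fixed. This is a worthwhile, inexpensive improvement and not a flaw in the primary outcome.

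**What to change.** - Keep the clinical/demographic baseline for the prediction claim.
- Preregister a second comparison in which the baseline matrix reasoning score is added to both the reference model and the task model.
- State in section 27 that, for overall response, a gain is read as evidence on a task's mechanisms only if it appears in this second comparison.
- Report a version that also includes symmetry span as a sensitivity analysis only.

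The cost is one more model in the same pipeline, using data already collected. Symmetry span was not given to the first 100 participants, but its imputation is already planned. If the score counts as a sixth predictor, the section 19 formula rises from 875 to 1,050, above the planned training set of 1,000; six lies within the article's own range of 4 to 6 predictors, and the planned penalised models soften the effect. Mechanistic claims for some tasks may become weaker. Some proxy gain will remain, because 12 items measure ability imperfectly, and the report should say so.

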### Trial design (12)

This is a randomized trial with two parallel intervention arms. Participants will be randomly assigned to either the Behavioral Activation (BA) group or the Cognitive Restructuring (CR) group in a 1:1 ratio. The primary goal of the study is to determine (1) which baseline characteristics predict the benefits (in terms of reduction of depression symptoms) each individual participant will receive from CBT-based interventions, and (2) which baseline characteristics moderate the therapeutic effects of BA and CR. Therefore, the study does not fall in the categorization of superiority, non-inferiority, or equivalence framework, and we do not make any assumptions regarding differences in overall treatment efficacy. We do not plan to establish efficacy, safety of feasibility. Instead, this is a mechanistic clinical trial aiming to uncover moderation of intervention effects.

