Previous research has demonstrated that e-couch is effective in reducing depressive symptoms, with meaningful within-subject effect sizes and modest-to-small between-group effects relative to control conditions (36–38). Notably, the BA and CR modules in e-couch were designed to reflect the core therapeutic strategies and mechanisms of change that underpin traditional face-to-face CBT. Following manuals of traditional CBT, both groups first learn about depression and treatment options in the psychoeducation module. In the CR interventions, participants then learn about biased ways of thinking that often occur in depression, how they can identify these, and how they tackle and change these biases. In the BA interventions, they learn about the role of rewarding activities in relation to mood, how to schedule and execute pleasant activities, and later, how they can incorporate more effortful and physical activities that will have a positive impact in the long run. The choice and order of modules was determined by two trained therapists on the study team ([name], [name]) and in discussion with collaborators who are also trained therapists. Through testing and a pilot study, we ensured that both arms require approximately the same amount of engagement and thus both interventions have a comparable dose. One advantage of delivering these components in a fully automated online format is that every participant receives the same standardized content, which enhances the fidelity of the intervention. Automation also minimizes the unintentional blending of strategies that can occur in therapist-delivered psychotherapy, where individual therapists may naturally shift between techniques or emphasize some elements over others. We will ask participants to repeat the core modules or submodules to ensure they thoroughly practice the skills they learn and reflect on them after trying them out in real life, mimicking procedures in therapist-delivered CBT.

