### Outcomes (16)

Our primary outcome is NOT a change in a specific symptom score or the superiority of one intervention over another. Instead, we aim to predict end-of-main-study (week 6) depression symptoms – both overall, and differentially for the BA and CR groups – in a held-out test dataset. Thus, our primary outcome is the out-of-sample predictive accuracy of improvement of depression symptoms using potential moderators. The prediction models will incorporate self-reported questionnaire data (clinical and demographic information) and computationally derived learning and decision-making variables from the behavioral tasks. Thus, our specific outcome depends on the exact target question and is tightly intertwined with the employed analysis approach. For more details on the specifications of the analysis approach and outcomes, see Section 27, *Statistical methods*. Also note that our primary outcome, as well as all trial estimands, will be precisely defined in the preregistration of the analyses of our untouched test dataset (and corresponding code). The separation of our data into a training and test dataset from the beginning of the study makes the specific definition of primary and secondary outcomes redundant at this stage.

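### In the pooled 'response to CBT' analysis, beating chance on the week-6 score says little about who benefits; the benchmark should be baseline severity and the aim worded as prognosis

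*Protocol article*

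**What the plan says.** Trial design (12) gives the first primary goal as finding "which baseline characteristics predict the benefits (in terms of reduction of depression symptoms) each individual participant will receive from CBT-based interventions". Outcomes (16) says that "our primary outcome is the out-of-sample predictive accuracy of improvement of depression symptoms". Sections 10 and 27a also speak of response to, or benefit from, CBT for the two arms taken together.

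The operational definition is under Primary analyses in section 27a. "For algorithms aiming to predict depression scores at week six" after either intervention, "the final outcome will be out-of-sample predictive accuracy above chance (for the baseline model"). The same sentence sets the bar for models with task data at the baseline model. The preceding text repeats the first benchmark: "Preregistered analyses of the test data will assess the extent to which this model improves predictive power as compared to chance". On the outcome variable it says "we will not use change scores as outcomes".

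The baseline model draws on clinical and demographic variables. Sample size (19) lists baseline severity among the candidate predictors, and section 27a leaves the final choice to automated selection and regularisation.

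On design, Trial design (12) says "This is a randomized trial with two parallel intervention arms". These are BA and CR, both delivered as e-couch modules. Section 15a reports that earlier e-couch trials showed "meaningful within-subject effect sizes and modest-to-small between-group effects relative to control conditions".

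**The concern.** The aim is about change due to an intervention. The criterion is about the level of the week-6 score, compared with no prediction at all. A person's depression score before the programme will usually say something about the score six weeks later, whether or not the programme helped. A model that captures only this persistence beats chance, and the result could be reported as confirmed prediction of benefit.

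The second problem is separate. Every participant in the pooled analysis receives a CBT module, so nothing in the data shows what would have happened without one. Natural recovery and regression to the mean stay mixed with treatment effect. The plan's own summary of earlier e-couch trials, with within-person change clearer than the difference from control, suggests that this mixture is not negligible.

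At stake is the reading of the first confirmatory test-set result. The abstract frames the work as helping to decide whether CBT is a good first-line choice for a given person, and a pass at this step would not support such a statement.

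**Working it through.** **Inputs from the protocol.** Section 19: Cox-Snell R2 0.05, response prevalence 0.5, shrinkage 0.9, 4–6 predictors, required n 875, test set of more than 300, 1,500 recruited, attrition about 20%. Abstract and section 27: 2:1 split.

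**Assumed.** Two-sided 5% level; baseline to week-6 correlation r between 0.1 and 0.6.

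**1. The plan's own figure.** The shrinkage criterion is n = p / [(S − 1) · ln(1 − R2/S)]. With S = 0.9 and R2 = 0.05, p = 4 gives 700, p = 5 gives 874.8 (rounded up to 875) and p = 6 gives 1,050. The stated 875 is reproduced with five predictors.

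**2. Test-set size.** 1,500 × 0.8 / 3 = 400; the protocol says more than 300. Both 300 and 400 are used.

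**3. Pass probability from one prognostic variable.** For the correlation between predicted and observed week-6 score, the probability of a significant result is Φ(atanh(r) · √(n − 3) − 1.96). For r = 0.2 and n = 300: atanh(0.2) = 0.2027, √297 = 17.23, product 3.49, less 1.96 = 1.53, so Φ = 0.94.

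**4. Simulation with no variation in benefit.** Each simulated participant has a baseline score (mean 12, SD 5), a week-6 score correlated r with it, and exactly the same benefit (4 points). The model holds baseline score only and is fitted in 1,000 training participants; 2,000 runs.

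| r | Formula, n = 300 | Formula, n = 400 | Simulation, n = 300 | Simulation, n = 400 |
|---|---|---|---|---|
| 0.1 | 41% | 52% | 41% | 53% |
| 0.2 | 94% | 98% | 93% | 98% |
| 0.3 | 99.96% | 100% | 99.95% | 100% |
| 0.4–0.6 | 100% | 100% | 100% | 100% |

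A correlation of 0.2 is 0.2² = 4% of week-6 variance. If 'above chance' meant only a test-set R2 above zero, the simulated pass rate at r = 0.1 would be 80% (n = 300) or 83% (n = 400).

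**5. Without an assumed correlation.** For a binary outcome with prevalence 0.5, a Cox-Snell R2 of 0.05 corresponds to an AUROC of about 0.63. With the Hanley-McNeil standard error, the probability of exceeding 0.5 significantly is 97% at n = 300 and 99% at n = 400. On the correlation scale, √0.05 = 0.224 gives 98% and 99.5%. This shows how easily the bar is cleared at the plan's own planning value; step 4 shows why clearing it says little about benefit.

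**6. The missing comparison.** Write the week-6 score as Y = Y0 − B, where Y0 is the score without the programme and B the benefit. A model in treated people estimates E(Y | X) = E(Y0 | X) − E(B | X). With no untreated arm the two terms cannot be separated, whichever benchmark is used. This applies to task variables as well. The difference between BA and CR at a given X is identified, because those two arms are randomised.

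**The case against.** A reader might infer that the first test cannot fail, or that the whole primary analysis is empty. The documents do not support either.

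- **The pass is not certain.** Baseline severity is a candidate, not a forced term. The correlation is assumed, and at r = 0.1 the pass probability is about even. Restricting the analysis to PHQ-9 above 4 (27b) may lower the correlation. The sample size section also works with a binary response, whose definition is left to the preregistration. The R2 of 0.05 was chosen from studies relating task behaviour to symptoms, so it is only a guide for a clinical model. What stands is 'likely to pass', under stated conditions.
- **Chance is the first of two steps.** Section 27a then asks whether each task adds accuracy above the baseline model. If severity has been selected, that comparison already holds it in the reference. It is not trivially passed and is much of what one would ask for.
- **The result is not a bare pass or fail.** The plan speaks of the extent of improvement over chance and will report error, R2 and AUROC with intervals. This softens the point, but 'above chance' is still named as the final outcome.
- **Efficacy is disclaimed.** Section 12 says so, and section 10 calls the trial a first step before independent trials. Not testing average efficacy, however, does not license statements about individual benefit.
- **Details are deferred to preregistration.** True for estimands and code, but the chance benchmark is already written down, and preregistration cannot supply an untreated arm.

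Declining to use change scores is not a fault: modelling the week-6 score with baseline as a predictor is sound. It does make baseline score, not chance, the natural reference.

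**Conclusion.** The point holds in a limited form and should be fixed before the test-set analysis is preregistered. For the pooled aim, the step-1 criterion is met with about 93–100% probability at 300–400 test participants if baseline severity is selected and r is about 0.2 or more, even with identical benefit for all. It is met with 97–99% probability at a Cox-Snell R2 of 0.05, and with only about 41–53% at r = 0.1. The correlation and the 5% level are assumptions.

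Passing step 1 therefore says little about improvement or benefit as sections 12, 16 and 27a use those words. Step 2 is informative, but about incremental prognosis under treatment. The Limitations section does not mention the lack of an untreated comparison. The randomised BA versus CR comparison is untouched by this point.

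**What to change.** - **Benchmark (27a, both places where chance is named).** Judge the baseline model against a frozen reference model, fitted in the training data, that contains only the baseline score of the outcome instrument. Report the incremental R2 and mean squared error, or AUROC for a binary outcome, in the test set. Comparison with chance can stay as description.
- **Step 2.** Keep baseline severity in the reference model for every task comparison, whatever automated selection does.
- **Wording (sections 10, 12, 16 and 27).** State pooled aim (1) as predicting week-6 depression given baseline severity among e-couch users, that is, prognosis. Reserve 'benefit more from' for the randomised BA versus CR contrast.
- **Limitations.** Add that without an untreated comparison the pooled models cannot separate treatment benefit from natural course.

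The cost is one extra reference model and some rewording, with no new data. The headline for the baseline model will look less favourable, because the increment over baseline score is a harder test than chance.
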